### Allocation

We will first divide the six wards into two groups, geographically apart. For each wave of two wards, we will randomly select one ward from each of these two groups. The first pair of wards to be selected will be wave 1, the second pair wave 2, and the third pair wave 3. Within each pair of wards, we will randomly allocate one to receive the video edutainment, while the other will receive basic home visits without videos. The home visits intervention will be obvious to households and health services in the wards receiving the visits. We will not attempt any blinding.

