### Data collection and analysis

The unit of randomization, intervention and analysis will be the ward. Information on outcomes (maternal morbidity, pregnancy behaviours and care, intermediate CASCADA variables) will come from the questionnaires about last completed pregnancies: from pregnant women delivering in wards receiving home visits, and from women reporting on their latest completed pregnancy at the baseline visit in the wards not yet receiving the home visits. The home visitors will also record maternal deaths.

To measure the impact of home visits compared with no home visits, we will contrast outcomes in wards receiving visits and those not yet receiving visits (wave 1 vs wave 2 in second year; wave 2 vs wave 3 in third year). The first round of home visits in wave 2 and wave 3 will provide the data for these waves as “controls” for the already visited waves (Fig. 2). To assess the impact of the added edutainment in the home visits, we will compare outcomes between the ward with basic visits and the ward with edutainment visits, within each wave. In total, we will compare 3 wards without edutainment with 3 wards with edutainment. We will use generalised estimating equations to incorporate the cluster design and differences at baseline, assuming an exchangeable correlation structure within wards [49].

In addition to the comparisons of proportions of outcomes between visited/not-visited wards and between video/non-video in visited wards, we will also undertake a more detailed analysis of intermediate outcomes in the CASCADA chain. We have previously done this in a cluster randomized controlled trial of community mobilisation for dengue prevention in Mexico [44]. This CASCADA analysis involves transitive closure treating the partial order as a bipolar weighted diagraph [50] with directed edges (arcs) from each factor to each later factor in the order. We convert these to input matrices by rescaling odds ratios from − 1 to 1, using the formula 1-(2/(OR + 1)) and submit these to fuzzy transitive closure using the ProbClosure package [51].

We will estimate the coverage of the home visits program in each ward by comparing the numbers in the submitted data with the population projections from the 2006 census, updated in the baseline household mapping exercise in each ward. We will also measure the proportions of pregnant women who received different numbers of the two-monthly follow up home visits.

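### Edutainment is drawn separately within each geographically split pair, so one allocation in four puts all three edutainment wards in the same geographic group

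*Protocol article*

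**What the plan says.** The Allocation section sets out three steps. The wards are first split by location: "We will first divide the six wards into two groups, geographically apart". Waves are then formed across that split: "For each wave of two wards, we will randomly select one ward from each of these two groups". Finally, edutainment is assigned inside each wave: "Within each pair of wards, we will randomly allocate one to receive the video edutainment". The other ward of the pair gets visits without the videos. No constraint across the three waves is stated.

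Under Data collection and analysis, edutainment is compared with basic visits inside each wave and the waves are then combined: "In total, we will compare 3 wards without edutainment with 3 wards with edutainment". The ward is named as the unit: "The unit of randomization, intervention and analysis will be the ward". The model is described in one sentence: "We will use generalised estimating equations to incorporate the cluster design and differences at baseline, assuming an exchangeable correlation structure within wards". Geographic group is not mentioned there.

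**The concern.** Taking one ward from each location for every wave balances geography for the home-visit comparison between waves. It does the opposite for edutainment. The two wards compared within a wave always come from different groups, so each of the three edutainment contrasts carries whatever separates the groups. If the video ward falls in the same group all three times, the edutainment comparison and the geographic comparison are the same comparison.

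The added value of edutainment is part of the second research question and has its own power statement. The Discussion also intends to draw a practical conclusion from a null result, namely that the extra cost is not justified. A 3:0 draw would weaken a conclusion in either direction, and no term for group added at analysis could repair it.

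**Working it through.** The article states no probability for this event, so there is no figure of its own to reproduce.

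**Inputs.** From Allocation: six wards, two groups, three waves with one ward per group in each (so three wards per group), and one edutainment ward per pair. From Data collection and analysis: a within-wave contrast, three wards against three in total. Assumption: the three draws are fair and independent, which is the natural reading.

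**1. Chance of a 3:0 split.** There are 3! × 3! = 36 ways to form the waves and 2³ = 8 edutainment draws, so 288 equally likely allocations.

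| Edutainment wards in group A | Allocations |
|---|---|
| 3 | 36 |
| 2 | 108 |
| 1 | 108 |
| 0 | 36 |

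P(all in one group) = (36 + 36)/288 = 2 × (1/2)³ = 25%. Choosing 3 of the 6 wards freely would give 2/20 = 10%, so the pairing raises the chance.

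**2. Can the two effects be separated?** Take a ward-level model with an intercept, two wave terms, group and edutainment (five columns).
- 3:0 split: correlation of edutainment with group ±1, rank 4 of 5. The edutainment effect is not estimable apart from group.
- 2:1 split: correlation ±1/3, rank 5 of 5. It is estimable, with 6 − 5 = 1 residual degree of freedom.

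**3. How much of a group difference d enters the contrast, before any baseline adjustment?**
- 3:0 split: d.
- 2:1 split: (2/3 − 1/3)d = d/3.
- The signs cancel over the allocations, so the average is zero.
- Mean square over the eight allocations: (2/8)d² + (6/8)(d/3)² = d²/4 + d²/12 = d²/3.
- Mean square over the six 2:1 allocations: d²/9.

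**4. Scale (assumed range).** The article gives no group difference. The planned edutainment effect, from Sample size, is 58% × 0.80 = 46.4%, then 46.4% × 0.85 = 39.4%, a difference of 7.0 points.

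| Assumed d (points) | Imbalance, 3:0 | Imbalance, 2:1 |
|---|---|---|
| 2 | 2 | 0.7 |
| 4 | 4 | 1.3 |
| 6 | 6 | 2 |

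These figures apply before baseline adjustment. The top of the range is generous. If k = 0.05 is read as a between-ward coefficient of variation (an assumption), the between-ward SD is 0.05 × 46.4 = 2.3 or 0.05 × 58 = 2.9 points. Even if all of that variation lay between the groups, d would be 2 × SD, that is 4.6 or 5.8 points.

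**5. Price of a group term after a 2:1 draw.** Ward-level residual degrees of freedom fall from 2 to 1, the two-sided 5% t value rises from 4.30 to 12.7, and the variance factor rises from 0.667 to 0.75. For the same residual SD the interval widens by (12.7 × √0.75)/(4.30 × √0.667) ≈ 3.1 times.

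**6. Is the restricted draw still fair?** Within any pair, 3 of the six 2:1 allocations give edutainment to the group A ward and 3 to the group B ward. Each ward keeps a 1/2 chance.

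**The case against.** The strongest reply is the planned adjustment for differences at baseline, stated directly after the edutainment comparison. Pre-visit data appear to exist: The intervention section has visitors ask each woman about her last pregnancy, and the first round in waves 2 and 3 is used as control data. A stable difference in level between the groups is what such adjustment targets, and this part of the reply stands. What adjustment cannot do after a 3:0 draw is separate the videos from group differences in time trend, in how visits are delivered, or in how households respond to them.

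A second reply is that a fair draw in each pair makes the contrast unbiased, and that any trial with six clusters risks chance imbalance. This is also true. A reader might infer that the edutainment estimate is biased by geography, perhaps by almost the planned effect. The documents do not support that: the realised allocation is not in the text, the design figure is not shown, the article gives no difference between the groups, and the figures in the scale table precede adjustment. What remains is that total aliasing, unlike ordinary chance imbalance, can be excluded in advance at almost no cost.

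A reader might also infer that leaving geographic group out of the model description is an error. It is not one: an article commonly leaves the full covariate list to the analysis plan, and with six wards a group term is a debatable choice.

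Finally, the pairing has a real merit, since it balances geography across waves for the home-visit comparison. The fix keeps it.

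**Conclusion.** The point holds as a weakness of the allocation scheme. With independent fair draws, the chance that edutainment is completely aliased with geographic group is exactly 25%. That figure and the rank result need no assumption about how far the groups differ. In the other 75% of allocations the effect can be separated from group, and an unadjusted contrast would carry one third of any group difference.

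Baseline adjustment limits the damage of a 3:0 draw to differential trend, delivery and response. The article gives nothing from which to size these. The finding concerns an avoidable chance confounding. It does not show that the trial drew an unbalanced allocation or that its edutainment result is biased.

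**What to change.** **If allocation is still open:** keep the geographic pairing, and draw the edutainment allocation at random from only the six allocations with a 2:1 split across the two groups. This takes one sentence in the Allocation section. The cost is 6 possible allocations instead of 8. The smallest two-sided randomisation p-value moves from 2/8 = 0.25 to 2/6 = 0.33, and neither could reach 5%. Exact balance is impossible with three pairs.

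**If allocation is done:** this is likely, since the Timeline places it at the start of the study and registration in August 2017 was retrospective. In that case report the realised split.
- If it is 3:0, rest the edutainment effect on each ward's change from its own first-round (pre-visit) data, and state that the remaining geographic confounding cannot be excluded. The cost is reliance on recalled earlier pregnancies as the baseline, and a more cautious conclusion.
- If it is 2:1, keep the planned baseline-adjusted comparison. A geographic-group term should be at most a sensitivity analysis, because it leaves a single ward-level residual degree of freedom.

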### Data collection and analysis

The unit of randomization, intervention and analysis will be the ward. Information on outcomes (maternal morbidity, pregnancy behaviours and care, intermediate CASCADA variables) will come from the questionnaires about last completed pregnancies: from pregnant women delivering in wards receiving home visits, and from women reporting on their latest completed pregnancy at the baseline visit in the wards not yet receiving the home visits. The home visitors will also record maternal deaths.

To measure the impact of home visits compared with no home visits, we will contrast outcomes in wards receiving visits and those not yet receiving visits (wave 1 vs wave 2 in second year; wave 2 vs wave 3 in third year). The first round of home visits in wave 2 and wave 3 will provide the data for these waves as “controls” for the already visited waves (Fig. 2). To assess the impact of the added edutainment in the home visits, we will compare outcomes between the ward with basic visits and the ward with edutainment visits, within each wave. In total, we will compare 3 wards without edutainment with 3 wards with edutainment. We will use generalised estimating equations to incorporate the cluster design and differences at baseline, assuming an exchangeable correlation structure within wards [49].

In addition to the comparisons of proportions of outcomes between visited/not-visited wards and between video/non-video in visited wards, we will also undertake a more detailed analysis of intermediate outcomes in the CASCADA chain. We have previously done this in a cluster randomized controlled trial of community mobilisation for dengue prevention in Mexico [44]. This CASCADA analysis involves transitive closure treating the partial order as a bipolar weighted diagraph [50] with directed edges (arcs) from each factor to each later factor in the order. We convert these to input matrices by rescaling odds ratios from − 1 to 1, using the formula 1-(2/(OR + 1)) and submit these to fuzzy transitive closure using the ProbClosure package [51].

We will estimate the coverage of the home visits program in each ward by comparing the numbers in the submitted data with the population projections from the 2006 census, updated in the baseline household mapping exercise in each ward. We will also measure the proportions of pregnant women who received different numbers of the two-monthly follow up home visits.

We will calculate the total cost of the home visits program, and extrapolate this to estimate the cost of introducing such a program for the whole of Toro LGA, and for the whole of Bauchi state. Using outcomes data, we will attempt to calculate the cost per maternal complication averted, allowing comparison with other programs. We will also calculate the incremental cost of the edutainment implementation strategy.

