**Methods:**

The trial will take place in six wards of Toro Local Government Area in Bauchi State, Nigeria, randomly allocated into three waves of two wards each. Home visits will begin in wave 1 wards immediately; in wave 2 wards after one year; and in wave 3 wards after a further year. In each wave, one ward, randomly allocated, will receive video edutainment during the home visits. Female home visitors will contact all households in their catchment areas of about 300 households, register all pregnant women, and visit them every two months during pregnancy, after delivery and one year later. They will use android handsets to collect information on pregnancy progress, send this to a central server, and discuss with the women the evidence about household factors associated with higher maternal risks, using video clips in the edutainment wards. Male home visitors will contact the partners of the pregnant women and discuss with them the same evidence. We will compare outcomes between wave 1 and wave 2 wards at about one year, between wave 2 and wave 3 wards at about two years, and finally between wards with and without added edutainment. Primary outcomes will be complications in pregnancy and delivery, and child health at one year. Secondary outcomes include knowledge and attitudes, use of health services, knowledge of danger signs, and household care of pregnant women.

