### Trial design

This is a pragmatic cluster randomized controlled trial (CRCT) in a stepped-wedge design [45, 46], anticipating further rollout after the project and in the meantime allowing us to compare maternal outcomes between wards randomly allocated to receive home visits early with those allocated to receive home visits after a delay (control wards). The two wards in wave 1 will be compared with the two wards in wave 2, and wave 2 wards will be compared with wave 3 wards.

Among wards receiving home visits, one half will be randomly allocated to receive basic home visits and the other half to receive visits plus edutainment (presentation and discussion of evidence-based video clips). We will therefore be able compare maternal outcomes between wards receiving home visits with and without the edutainment element.

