### Sample size

Our sample size calculations use the clinical trials simulator of Taylor and Bosch [48]. Maternal morbidity and intermediate outcomes in the CASCADA model are common so the study will have power to detect quite small shifts in these outcomes. Our 2013 study found 60% of Toro women did not reduce heavy work in pregnancy and 58% had evidence of post-partum infection or another serious complication of pregnancy [32]. At this level of occurrence, based on an estimated 2880 births in each ward over a two year period, our study will be able to detect a 20% reduction in complications (80% power at the 5% level, k = 0.05) between the home visit wave 1 wards and the next two wards before they start visits (wave 2).

Assuming the visits do reduce post-partum infection by 20%, a comparison of the three wards with visits plus edutainment versus the three with basic home visits would be able to detect a further improvement of 15% (80% power at 5% level, k = 0.05).

The study is not powered to show an impact on maternal mortality, although this should be measurable with later rollout to other LGAs. The Toro MMR of around 800 per 100,000 live births implies around 35 maternal deaths in each ward over a two year period. The wards with universal home visits would have to reduce mortality by 35% to be detected with 80% power at the 5% level (k = 0.06). Assuming the universal home visits reduced mortality risk by this amount, the video edutainment would need to reduce this by a further 60% for this to be detected across three dyads with 80% power at the 5% level.

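### The home-visit effect is specified as two separate 2 v 2 ward contrasts with no pooled estimate, although combining them would cut the standard error from about 3.2 to 1.7–2.0 points

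*Protocol article*

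**What the plan says.** The Trial design section states: "This is a pragmatic cluster randomized controlled trial (CRCT) in a stepped-wedge design". The six wards are "randomly allocated into three waves of two wards each" (Abstract, Methods). Under Data collection and analysis, "we will contrast outcomes in wards receiving visits and those not yet receiving visits", and the contrasts are listed as "wave 1 vs wave 2 in second year; wave 2 vs wave 3 in third year". The Abstract and the Trial design section describe the same two pairs. Control data for waves 2 and 3 come from their own first round of visits.

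The Sample size section powers only the first pair, "between the home visit wave 1 wards and the next two wards before they start visits (wave 2"). The same Data collection and analysis section says that generalised estimating equations (GEE) with exchangeable within-ward correlation will allow for clustering and for differences at baseline. It does not say whether one model covers both contrasts, and it names no overall home-visit effect.

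**The concern.** Home visits are the main intervention, and the article commits to two answers about them without saying how they become one. Each answer rests on four wards. Wave 2 contributes to both with opposite sign, so the estimates are negatively correlated. That makes them more likely to disagree than two independent estimates would be, and makes their average more precise. If they are reported side by side, that precision is lost and a reader may stress whichever result is more favourable.

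There is a related gap. For wave 1 v wave 2, the first-round outcome in wave 2 is its control outcome, so that outcome cannot also serve as the baseline for which the comparison is adjusted.

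**Working it through.** **Inputs.** Prevalence: "58% had evidence of post-partum infection or another serious complication of pregnancy". Births: "based on an estimated 2880 births in each ward over a two year period", taken as 1440 per ward-year. Target: "our study will be able to detect a 20% reduction in complications (80% power at the 5% level, k = 0.05"), that is 58% to 46.4%, a difference of 11.6 points. Assumed, because the article does not give it: the correlation r of a ward's true rate between years, from 0.5 to 1.0.

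**Step 1, the article's own figure.** The unmatched Hayes–Bennett formula gives wards per arm c = 1 + (1.96 + 0.84)² × [p0(1-p0)/n + p1(1-p1)/n + k²(p0² + p1²)] / (p0 - p1)². With unrounded normal quantiles the first factor is 7.849:

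c = 1 + 7.849 × [0.000169 + 0.000173 + 0.0025 × (0.3364 + 0.2153)] / 0.01346 = 2.00.

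This reproduces two wards per arm and confirms that k is a coefficient of variation. Read as an intraclass correlation, it would need about 15.6 wards per arm.

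**Step 2, one contrast.** With 58% in both arms, the between-ward variance is t² = (0.05 × 0.58)² = 0.000841 and the sampling variance is s² = 0.58 × 0.42 / 1440 = 0.000169. The variance of a 2 v 2 difference is 2 × (t² + s²)/2 = 0.00101, so SE = 0.0318. Using 46.4% in the visited arm gives 0.0293.

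**Step 3, both contrasts.** Their correlation is -(r × t²/2)/(t² + s²) = -0.416r. With period effects fitted and only these cells used, generalised least squares reduces to the plain average, with SE = 0.0318 × √[(1 + correlation)/2]. The last two columns add further visited cells under a single visited/not-visited effect.

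| r | Correlation | One contrast | Two combined | + wave 1 at step 2 | + final all-visited year |
|---|---|---|---|---|---|
| 1.0 | -0.42 | 0.0318 | 0.0172 | 0.0148 | 0.0109 |
| 0.8 | -0.33 | 0.0318 | 0.0184 | 0.0180 | 0.0149 |
| 0.5 | -0.21 | 0.0318 | 0.0200 | 0.0199 | 0.0186 |

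Combining divides the SE by 1.85 (0.0318/0.0172) to 1.6 (0.0318/0.0200). Restoring wave 1 at the second step then removes about 14%, 2% and 0.3% at r = 1.0, 0.8 and 0.5. At k = 0.10, one contrast has SE 0.0594 and the combination 0.0304 to 0.0367.

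**Step 4, what this means for the target.** The article makes the ward the unit of analysis, so one contrast has 2 degrees of freedom (t = 4.303). Its 95% half-width is 4.303 × 3.18 = 13.7 points (12.6 with SE 0.0293), wider than the 11.6-point target, and power is about 50% to 56%. For the pooled estimate, 4 degrees of freedom (assumed) give 2.776 × 1.72 = 4.8 to 2.776 × 2.00 = 5.6 points. With 3 degrees of freedom (t = 3.182), the half-width is 5.5 to 6.4 points.

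**Step 5, the cost of adding longer exposure.** At r = 0.8 the single-effect model on all cells puts weights of 1.28, 0.09 and -0.36 on the first-, second- and third-year effects. If benefit grows with exposure, that model understates it.

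**The case against.** The planned contrasts are concurrent randomised comparisons. Both set wards in about their first year of visits against unvisited wards, so they need no assumption that the effect is constant over exposure time, and the sample size matches the first of them. Model details are commonly left to an analysis plan, which is not shown. The GEE sentence does not exclude one joint fit, and household demographics and socio-economic status, collected at the first visit (The intervention), allow adjustment for covariates. All of this stands. What remains is that three sections fix the comparison as two pairs and none names a combined effect.

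A reader might infer three stronger criticisms that the article does not support:

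- **That leaving wave 1 out of the second step is the main loss.** It is not: at r of 0.8 or below it costs 2% of the SE or less. Wave 1 visits also pass to government running in years 3–4 (Knowledge translation and exchange), which may overlap the third-year comparison.
- **That the plan's standard error is twice what the data allow.** That ratio compares one contrast with all the data and depends on r.
- **That all within-ward information is discarded.** The stated GEE could use wave 2's change if it were fitted jointly.

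**Conclusion.** The concern holds as a matter of precision and clarity. As written, the plan yields two weak, negatively correlated home-visit estimates (SE about 3.2 points each) where one pooled estimate from the same cells would have SE 1.7 to 2.0 points. This rests on 58% prevalence, 1440 births per ward-year, k = 0.05 as a coefficient of variation, and r between 0.5 and 1.0. A larger k raises every figure, but the advantage of combining remains. The planned contrasts are not biased by being analysed separately. A constant-effect model over all ward-periods would be a trade-off rather than a free gain, and the pairwise contrasts could not check its assumption because neither contains longer exposure.

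**What to change.** Before outcomes are examined, state that:

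- The primary home-visit analysis is one pooled estimate of the two planned same-period contrasts. It comes from one model with calendar-period effects that accounts for wave 2 wards appearing in both (a ward effect or ward-level correlation), with a small-sample correction for six wards.
- The two contrasts are also shown separately, as supportive results.
- Baseline adjustment in wave 1 v wave 2 uses covariates only, because wave 2's first-round outcome is its control outcome.
- Adding wave 1 at the second step and the final all-visited year is a sensitivity analysis. It assumes an effect constant over exposure time and overlaps the government-run period in wave 1. Wave 1 at the second step gains little unless r is near 1.

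The cost is analysis wording; no new data are needed. The downside is that pooling assumes a common first-year effect at both steps. The separate contrasts can check this, but only roughly: the SE of their difference is 0.0318 × √[2 × (1 + 0.33)] = 0.052 at r = 0.8.
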